### Subsample size calculation

Given the resource constraints, only a subsample will be studied for the analysis of circadian melatonin and cortisol rhythm from saliva samples. Subsample size is calculated using G*Power software, with expected effect size of 0.82, type I error rate of 0.05 and a desired power of 0.95 [13]. The total subsample size is 80 as calculated using G*Power software. To compensate for non-compliance and non-response among pregnant women, the subsample size is increased (+ 20%) to 100.

### Study measurements

Socio-demographic background of subjects, which include their age, ethnicity, educational level, occupation, household income and health history will be obtained through a questionnaire at recruitment. Table 1 shows the details of the variables assessed at each follow-up in this study.

**Table 1 Tab1:** Summary of data collection and timeline

	Prenatal			Postnatal		
Data	Recruitment	2nd trimester	3rd trimester	Delivery	6 months	12 months
Mothers						
Sociodemographic	•					
Date of birth	•					
Ethnicity	•					
Marital status	•					
Educational level	•					
Occupation	•					
Monthly household income	•					
Health history	•					
Pre-pregnancy BMI	•					
Weight at assessment		•	•			
DASS-21		•	•			
3-day food record		•	•			
Pittsburgh Sleep Quality Index		•	•			
Social jetlag		•	•			
Morningness-Eveningness Questionnaire		•	•			
Salivary sample		•	•			
Step counts		•	•			
Neonatal Questionnaire				•		
Infant						
Sex				•		
Mode of delivery				•		
Birth weight				•		
Length at birth				•		
Head circumference at birth				•		
Infant feeding practice					•	•
Weight					•	•
Length/height					•	•
Head circumference					•	•
Waist circumference					•	•
Mid-upper arm circumference					•	•
Subscapular skinfold thickness					•	•
Triceps skinfold thickness					•	•

### Exposures measures

#### Circadian rhythm

Circadian rhythm of pregnant women will be assessed using both subjective and objective measurements during second and third trimester of pregnancy. Subjective measurement of chronotype (morning and evening types) will be collected using Morningness-Eveningness questionnaire (MEQ) while objective measurement of circadian rhythm will be determined from salivary melatonin and cortisol rhythm of pregnant women. Chronotype refers to the expression of circadian rhythmicity that may vary among individuals [14]. It was demonstrated in past studies that different chronotypes exhibit vary circadian rhythms of several physiological variables [14]. Besides, sleep parameters are useful as phase markers of the circadian rhythm as well, given that sleep/wake cycle is an important aspect of circadian rhythm [5]. In this study, sleep disturbances and quality of pregnant women during second and third trimester will be determined using Pittsburgh Sleep Quality Index (PSQI) Questionnaire.

##### Morningness-Eveningness questionnaire

The Morningness-Eveningness Questionnaire (MEQ) is the most widely used questionnaire to differentiate individuals with extreme circadian tendencies [15]. This questionnaire is frequently used to correlate with core parameters of human circadian organization such as the timing of sleep and predict the endogenous circadian phase [5, 15]. The MEQ score is negatively correlated with the objective phase marker in which subjects with a later circadian phase generally scored lower on the MEQ [15]. The MEQ contains 19 questions, most of which elicit preferences in timing of daily activities and sleep. Most questions in MEQ are designed in a preferential manner where respondent is asked to indicate his/her preferred time of rising and bedtime, as well as physical and mental performance and alertness after rinsing and after different activities [16, 17]. This questionnaire comprises of five behavioral categories: definitive morning (score = 70–86), moderate morning (score = 59–69), neither types (score = 42–58), moderate evening (score = 31–41) and definitive evening (score = 16–30).

##### Salivary melatonin and cortisol rhythm

In the present study, melatonin and cortisol will be measured using saliva samples. Both melatonin and cortisol can be measured in saliva in their free form [7]. Salivary concentrations have been shown to give an accurate indication of free or biologically active melatonin and cortisol as compared to human serum [5, 18]. Measuring salivary melatonin and cortisol can be used to characterize production patterns over each 24-h study period to facilitate comparisons between individual. Moreover, saliva is preferable to serum as a non-invasive alternative to determine melatonin and cortisol level. The taking of blood can cause variation in salivary cortisol level due to the effect of stress [7, 19].

Passive drool method will be used whereby subjects need to tilt their head forward and drooled through a funnel into a centrifuge tube [20]. Saliva sample collection will be taken at 2 time points during pregnancy, at second and third trimester respectively. The first sampling process will start at awakening in all cases, followed by 9:00, 15:00, 21:00 and 03:00 taken at 6 hourly intervals over the 24-h period. This will be done by subjects themselves and each subject will receive individual education regarding the collection process prior to the start of the data collection. To avoid saliva sample contamination with food, subjects are advised to refrain from eating a major meal or brushing their teeth with toothpaste within 30 min of sample collection [21, 22]. No chocolate or bananas, alcohol, caffeine, nicotine or drinks with artificial colorants should have been taken within the prior 12 h and on the day of sampling [21–23].

During the daytime sampling, saliva samples will be collected under normal light conditions. To minimize light interference with the secretion of salivary hormones, subjects are required to carry out the entire procedure in dim light for collection timed at 03:00 and 21:00 [24]. Subjects will be reminded not to cough up mucus during saliva collection. The centrifuge tube will be covered with aluminium foil and marked with a red line to emphasize the 3 mL marking. After each collection, the tube containing the saliva sample will be placed in a labelled resealable bag in the family’s freezer. Subjects are required to label the tube with the sampling time and date. Subjects will be encouraged to report their actual sampling times, even if there is deviation from the given protocol. Subsequently, the bag with saliva samples will be collected from the subject. The samples will then be centrifuged upon returning to the lab. Supernatant solution will be collected after centrifugation and stored in a − 20 °C freezer until further analysis. Concentration of salivary melatonin and cortisol will be determined using ELISA kit according to manufacturer-provided standards and protocols. Flowchart illustrating the procedures of passive drool method is shown in Fig. 2.

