## Discussion

Pregnancy is a critical period when the system and organs of a new human body develops. Any disruption to the environment in which the fetus grows may result in developmental adaptations that produce permanent alterations to structural and physiological metabolic functions of the fetus [58, 59]. A hypothesis proposed in 1990 by the British epidemiologist David Barker, known as the Barker hypothesis, states that the environment during embryonic and fetal development increases the susceptibility of developing certain postnatal diseases later in life [60]. These effects are referred to as fetal programming which highlights the potential link between maternal factors on fetal growth and subsequently, infant health.

Pregnancy is considered as a period susceptible to chronodisruption as pregnant women often undergo physical, physiological, social and emotional changes, which may alter their usual lifestyle. Sleep problems such as insomnia and sleep deficiency are among the common issues reported during pregnancy due to various factors such as endocrine changes, backache, increase in size, fetal movement, frequent urination, leg cramps, abdominal discomfort, heartburn and vomiting [61, 62]. Sleep/wake cycles are closely intertwined with the circadian system, and disrupted sleep during pregnancy could potentially affect maternal circadian rhythm [5]. Furthermore, due to the lifestyle modernization and common use of artificial lightning, problem of disrupted or irregular circadian rhythm is not limited to shift worker, but may pose a significant health risk on the general public as well.

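### At 21:00 the dim-light rule covers only the collection itself, so it does not protect the melatonin secreted beforehand, and fitted acrophase is sensitive to that sample

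*Protocol article*

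**What the plan says.** The section on salivary melatonin and cortisol rhythm gives the sampling scheme: "The first sampling process will start at awakening in all cases, followed by 9:00, 15:00, 21:00 and 03:00". Women collect the samples themselves at home, in the second and again in the third trimester.

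The light rule has two parts. For daytime, "During the daytime sampling, saliva samples will be collected under normal light conditions". For the two night-time points, the purpose is stated as "To minimize light interference with the secretion of salivary hormones", and the measure is that "subjects are required to carry out the entire procedure in dim light for collection timed at 03:00 and 21:00". The same paragraph ends with "Flowchart illustrating the procedures of passive drool method is shown in Fig. 2", which ties the word *procedure* to the drooling and handling steps.

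Other influences on the sample have explicit lead times. Women are told to "refrain from eating a major meal or brushing their teeth with toothpaste within 30 min of sample collection", and none of a list of foods and drinks "should have been taken within the prior 12 h and on the day of sampling". The text gives no lead time for light. The tube label carries only the sampling time and date.

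Under Statistical analysis, melatonin baseline, acrophase and amplitude are derived from these samples. They are compared between trimesters by paired t-test and related to stress, step count and eating behaviour.

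**The concern.** The stated aim is to protect *secretion*. That is different from protecting the sample from light, which the foil around the tube may do. Hormone found in saliva at 21:00 reflects secretion over the time leading up to 21:00, so dimming the light at the moment of collection comes too late to alter most of it.

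At stake is melatonin phase in the saliva subsample (80 women required, 100 planned). If evening light lowers the 21:00 value in some women, their fitted peak moves later although their underlying rhythm need not differ. The second-versus-third-trimester comparison would take in the difference between two uncontrolled evenings. If evening light also differs between women who do and do not eat late, part of an association under Objective 2 could come from lighting. The documents neither show nor exclude that link, so it is a possibility only. The text shows no record of evening light, so it could not be adjusted for afterwards.

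**Working it through.** The plan gives no figure on this point, so there is none to reproduce. The check is a reading of the text followed by two illustrations on assumed inputs.

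**1. Rule against purpose**

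| Influence | Stated control before the sample |
|---|---|
| Major meal, toothpaste | 30 min |
| Listed foods and drinks | 12 h and the sampling day |
| Light, 21:00 and 03:00 | none; dim light during the procedure |

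Bright light until 20:59, then dim light for the collection, is full compliance.

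**2. How much of the 21:00 hormone predates the dim period**

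Assumptions, not in the documents: first-order clearance, half-life T of 20 to 60 min, collection lasting t = 5 to 20 min. The share of melatonin present at the start that is still there at the end is 2^(−t/T).

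- t = 5, T = 60: 2^(−5/60) = 0.944
- t = 10, T = 45: 2^(−10/45) = 0.857
- t = 20, T = 20: 2^(−1) = 0.50

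Between half and 94% remains at the end. If dim light began 60 min earlier, with T = 30 to 60 min, only 2^(−60/30) = 0.25 to 2^(−60/60) = 0.50 would date from before it.

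**3. How far the fitted phase depends on the 21:00 value**

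From the protocol: samples at awakening, 09:00, 15:00, 21:00 and 03:00. Assumed: awakening 06:30, a 24-hour cosine with mesor 10, amplitude 8 and true peak at 03:00 or 02:00, and least-squares fitting. The model is y(t) = M + A·cos(2π(t − φ)/24). Only the 21:00 value is multiplied by (1 − s).

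| Reduction s at 21:00 | Peak 03:00: fitted acrophase (shift) | Amplitude | Peak 02:00: fitted acrophase, hours (shift) | Amplitude |
|---|---|---|---|---|
| 0 | 3.00 | 8.00 | 2.00 | 8.00 |
| 25% | 3.56 (+0.56 h) | 8.02 | 2.67 (+0.67 h) | 7.68 |
| 50% | 4.10 (+1.10 h) | 8.21 | 3.38 (+1.38 h) | 7.61 |
| 75% | 4.61 (+1.61 h) | 8.56 | 4.07 (+2.07 h) | 7.80 |

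With awakening varied from 06:00 to 07:00, the shifts span 0.54 to 2.12 hours and amplitude stays between 7.6 and 8.6. With the 03:00 peak and awakening at 06:30, the fitted mesor falls from 10 to 9.32, 8.65 and 7.97.

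**4. Influence of each sample**

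In the same model (peak 03:00, awakening 06:30), lowering one value by one unit moves acrophase by:

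- 21:00: +13 min
- 09:00: −10 min
- awakening: −7 min
- 03:00: +4 min
- 15:00: almost nothing

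The 21:00 sample is the most influential single point, but the two morning samples together (10 + 7 = 17 min) outweigh it.

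**The case against.** The strongest objection is that this is a condensed article. Figure 2, which shows the collection steps, is not available here. Each woman receives individual education, the kit contains instructions, and the source cited for the light rule cannot be seen. A lead-in period may be stated in any of these. This stands as a limit: the finding concerns the rule as the text words it. It is still more than missing detail, because the article states both a purpose and a measure, and at 21:00 the measure does not serve the purpose.

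Second, the cohort is observational and concerns ordinary pregnant women. The Discussion notes that "due to the lifestyle modernization and common use of artificial lightning, problem of disrupted or irregular circadian rhythm is not limited to shift worker", so habitual evening light may be part of what is being studied, and imposing dim light would change what the 21:00 value represents. That is a legitimate choice, but it conflicts with the stated aim of minimizing light interference, so the plan should say which is meant.

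Third, changing an instruction after recruitment began in June 2019 could put one woman's two trimesters under different rules. This stands and is dealt with in the fix.

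Stronger readings are tempting but not supported:

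- A reader might take the 50% to 94% in step 2 as the share of the reading distorted by light. It is only the share of hormone already present when collection starts, and would be the same if light suppressed nothing.
- A reader might extend the point to amplitude. The illustration shows little change, and the plan defines amplitude from daytime baseline to peak, to which 21:00 contributes little.
- A reader might say the 21:00 value decides whether the peak is early or late. Step 4 shows that it does not do so alone.
- A reader might condemn the rule as a whole. It says minimize, not eliminate, and at 03:00 it is largely adequate.
- Nothing in the documents extends the point to the cortisol slope.

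**Conclusion.** The concern holds for melatonin phase from the 21:00 sample in the saliva subsample. As worded, the rule restricts light too late to protect the secretion that this sample measures, although the same section sets lead times for food and toothpaste.

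If evening light lowers the 21:00 value by 25% to 75%, the fitted acrophase moves about 0.5 to 2.1 hours later, with amplitude near 8. This rests on an assumed cosine rhythm (mesor 10, amplitude 8, peak 02:00 to 03:00, awakening 06:00 to 07:00) and on assumed reductions. The true suppression, and so the actual bias, cannot be obtained from the documents. That most women are asleep before 03:00 is also an assumption, though a reasonable one with shift workers excluded.

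This is a minor, worthwhile improvement. It does not touch the main cohort's questionnaire measures or the birth and infant outcomes themselves.

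**What to change.** - Extend the dim-light instruction to a stated period before the 21:00 sample, for example 60 minutes with screens off or dimmed, as well as during collection. If the participant materials already contain such a period, state it in the text. The 03:00 rule needs no addition.
- Add a tick-box to the tube label for whether this was followed.
- Run the melatonin acrophase analysis with and without non-compliant 21:00 samples.
- Because recruitment is under way, record which instruction applied to each sample, and check the second-versus-third-trimester comparison within women sampled under the same instruction both times.
- If habitual evening light is what the study intends to capture, record it, describe the 21:00 value as measured under habitual light, and reword the stated purpose.

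The cost is an instruction line, a label change and one sensitivity analysis, plus one hour of restricted light on two evenings for each woman in the subsample. Restricting the trimester check to women under one instruction will reduce the number of pairs in that check.

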**Fig. 2 Fig2:**
[figure not shown]
Flowchart of saliva sample collection by passive drool method

##### Pittsburgh sleep quality index questionnaire

Pittsburgh sleep quality index (PSQI) is a self-rating questionnaire that measures sleep quality and disturbances over a 1-month period [25]. PSQI contains 19 items which summarize 7 clinically derived components of sleep quality and patterns: subjective sleep quality, sleep latency, sleep duration, sleep efficiency, sleep disturbances, use of sleep medication and daytime dysfunction. These items are scored from 0 to 3, and then added together to calculate a total PSQI global score ranging from 0 to 21. It was reported in past studies that the PSQI has similar psychometric properties in both non-pregnant populations and pregnant women [26]. The PSQI has been used on pregnant Asian women in previous studies [26–28]. A validated Malay version of PSQI will be used in the study [29]. The established cutoff of above 5 will be used in this study to depict poor sleep quality in pregnant women. Additionally, bedtime and awake time on workdays and work-free days will be obtained to assess social jetlag (SJL). SJL is calculated as the absolute difference between mid-sleep on work-free days and mid-sleep on workdays [30].

#### Depression, anxiety, and stress scales (DASS-21) questionnaire

The Depression, Anxiety and Stress Scale - 21 Items (DASS-21) is a set of three self-report scales designed to measure the emotional states of depression, anxiety and stress. DASS-21 contains three subscales that cover depression (7 items), anxiety (7 items), and stress (7 items). Each item is scored from 0 (at all) to 3 (very much). Final score of each subscale will be multiplied by two (× 2) as DASS-21 is short form version of DASS which has 42 items. The final scores will be classified into different level of severity: normal, mild, moderate, severe and very severe. A valid Malay version of DASS-21 will be used in current study [16]. DASS-21 has been applied in past studies involving pregnant Asian women, including Malaysian pregnant women [17, 31].

#### Measurement of physical activity

Omron HJ-321 pedometer will be used to measure relative step count in pregnant women. It has been shown to produce accurate measurement of physical activity in the past studies [32–35]. Pedometer is a cost-effective alternative for objective measurement of physical activity and able to capture low-intensity activities including walking [36]. Walking has been reported to be the most popular form of activity for pregnant women in various studies [37–39].

Measurement of relative step count of pregnant women will be taken during second and third trimester. Pedometer readings will be accumulated for a 5 consecutive days during waking hours (excluding water activities), including at least one weekend day, which has previously shown to be sufficient for estimating weekly physical activity [40]. The pedometers will be programmed to an average stride length of 50 cm as used in the previous study [39]. Subjects will be instructed to carry the pedometer around the neck with a lanyard for 5 days to record activity data. They will be given a simple exercise diary to record their daily step count. Pregnant women are encouraged to maintain their normal daily activities to reduce reactivity bias. A full day was considered as wearing the pedometer for at least eight daytime hours and a half day was considered as < 8 h but more than 3 h. If worn for < 3 h a day, this was treated as a missing day. Step count measured by the pedometer will be classified as followed: < 5000/day as “sedentary”, 5000–7499 steps/day as “low active”, 7500–9999 as “somewhat active” and > 10,000 as physically active based on the criteria proposed by [41].

#### 3-day food record

A 3-day food record will be used to record timing of meals taken, type of food or beverage and the amount consumed. Dietary intakes will be assessed for 3 non-consecutive days within a week, comprising two weekdays and one weekend day as the dietary pattern may vary on weekday and weekend day. Subjects will be given instructions on how to record their food intake. Subjects will be encouraged to include detailed descriptions of all foods and beverages including cooking methods, estimated portion size and brand of processed foods and beverages consumed for the past 24 h. Estimation of foods consumed based on household measurement such as cups, plates and tablespoons will be required. To minimize recall bias, subjects will be educated by trained interviewers and they are advised to self-record their diet a the time the food are eaten.

Data that will be identified from the 3-day food record includes eating behaviors including breakfast-skipping, late-night eating and intermittent fasting. Energy and nutrient distribution among the meals will be tabulated. Duration of the last meal of the day to sleeping time will be calculated. Meal frequency as well as eating window will be assessed. Eating window is defined as the time interval between first and last energy-containing meal taken for the day [42].

The estimated amount consumed will then be converted into grams. The mean values for energy and nutrient intake for the three days will be calculated. Malaysian Food Composition Tables [43] and ASEAN Food Composition Tables [44] will be used in dietary analysis. The mean values for energy and nutrient intake will be analyzsed using Nutritionist Pro (First Data Bank Inc., 2011) and then compared with Recommended Nutrient Intake (RNI) for pregnant women [45] to determine intake adequacy. All results will be presented as means, standard deviations and percentages. Ratio between reported total energy intake (EI) and basal metabolic rate (BMR) will be calculated to identify under-reporting of energy intake. BMR is calculated using the BMR equation for Malaysian adults and additional energy requirements during pregnancy will be included in the calculation: 280 kcal/day for second trimester and 470 kcal/day for third trimester [46]. Golderg cut-off point for under-reporting of EI (EI/BMR ratio < 1.2) will be used [47].

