## Methods/design

### Study aims

The aim of the study is to determine the association of stress, physical activity and chrononutrition with circadian rhythm among pregnant women and its impact on total gestational weight gain, birth and infant outcomes. To achieve the aim, the specific research objectives to be investigated in the study are:
To determine the circadian rhythm of pregnant women in Kuala Lumpur, Malaysia.To determine the association of stress, physical activity and chrononutrition (energy and nutrient intake, energy and nutrient distribution, meal frequency, eating window, breakfast-skipping, late-night eating and intermittent fasting) with circadian rhythm among pregnant women.To determine the association of irregular circadian rhythm with total gestational weight gain, birth outcomes (birth weight, gestational age at birth and delivery method) and infant outcomes (infant weight, body composition and temperament).

The hypothesis is that mothers with irregular circadian rhythm during pregnancy are associated with higher risk of poor birth outcomes and have unfavorable outcomes, especially on the infant growth and temperament in later life.

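### Judging nutrient adequacy by setting unadjusted 3-day mean intakes against the RNI would overstate inadequate intake, by an amount the article does not allow one to fix

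*Protocol article*

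**What the plan says.** The section 3-day food record of the protocol article sets out the dietary method. On recording: "Dietary intakes will be assessed for 3 non-consecutive days within a week, comprising two weekdays and one weekend day". On the summary: "The mean values for energy and nutrient intake for the three days will be calculated". These means, for energy and for nutrients alike, are "then compared with Recommended Nutrient Intake (RNI) for pregnant women [45] to determine intake adequacy". On reporting: "All results will be presented as means, standard deviations and percentages".

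The same section adds a check on reporting quality: the "cut-off point for under-reporting of EI (EI/BMR ratio < 1.2) will be used". That check flags women whose energy intake looks implausibly low. It changes neither the reference value nor the meaning of adequacy.

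The section names no average requirement and no adjustment from a 3-day mean to usual intake. It gives no RNI values and no definition of the RNI.

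**The concern.** The article fixes three things: the quantity compared (an unadjusted 3-day mean), the yardstick (the RNI) and the conclusion to be drawn (adequacy). A recommended intake is a suitable target for an individual woman. It is a poor cut-off for counting how many women fall short if it is set high enough to cover nearly everyone. A woman between the average requirement and the RNI is then more likely than not to meet her own need, yet she would be counted as inadequate.

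A second, separate problem is that a mean of three days carries day-to-day variation. Its distribution is wider than that of usual intake, which distorts the share of women on either side of any cut-off, whatever the cut-off means.

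At stake is a descriptive figure: the proportion of pregnant women in Kuala Lumpur reported as having inadequate intake of a given nutrient.

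**Working it through.** The article states no prevalence of inadequacy, so there is no figure to reproduce. The check asks how far a count below the RNI departs from the share of women below their own requirement. **All numerical inputs are assumptions**; the article supplies only the rule and the number of recorded days (three).

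**Model.** Requirement is normal with mean 1 and CV c. Usual intake is normal with mean m and between-woman CV b, independent of requirement. RNI = 1 + 2c, which covers about 97.7% of women. Day-to-day CV is w.

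- Truly inadequate: Φ((1 − m) / √((b·m)² + c²))
- Counted as inadequate by the RNI: Φ((RNI − m) / (m·√(b² + w²/3)))
- Below the average requirement on the 3-day mean: Φ((1 − m) / (m·√(b² + w²/3)))

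**Step 1: mean intake equal to the RNI.** The RNI count is then 50% whatever b and w are.

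| c | RNI = m | b | SD of intake | SD of (intake − requirement) | z | Truly inadequate | Ratio of 50% to truth |
|---|---|---|---|---|---|---|---|
| 10% | 1.2 | 20% | 0.24 | 0.260 | −0.2/0.260 = −0.769 | 22.1% | 2.3 |
| 10% | 1.2 | 30% | 0.36 | 0.374 | −0.2/0.374 = −0.535 | 29.6% | 1.7 |
| 15% | 1.3 | 20% | 0.26 | 0.300 | −0.3/0.300 = −1.0 | 15.9% | 3.1 |
| 15% | 1.3 | 30% | 0.39 | 0.418 | −0.3/0.418 = −0.718 | 23.6% | 2.1 |

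**Step 2: other mean intakes, with day-to-day variation** (c = 10%, b = 30%, w = 30%, RNI = 1.2). The SD of the 3-day mean is m·√(0.09 + 0.09/3) = 0.346·m.

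| m (× average requirement) | Truly inadequate | 3-day mean below average requirement | 3-day mean below RNI | Ratio, RNI count to truth |
|---|---|---|---|---|
| 0.8 | 77.9% | 76.5% | 92.6% | 1.19 |
| 1.0 | 50.0% | 50.0% | 71.8% | 1.44 |
| 1.2 | 29.6% | 31.5% | 50.0% | 1.69 |
| 1.5 | 13.9% | 16.8% | 28.2% | 2.03 |
| 1.8 | 7.3% | 10.0% | 16.8% | 2.31 |

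The average-requirement cut-off stays within 3 percentage points of the truth here, and what remains comes mostly from day-to-day variation. The RNI count is 9.5 to 21.8 points too high.

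**Step 3: a wider grid.** c = 10% or 15%; b = 20%, 30% or 40%; w = 0%, 30% or 50%; m at eight values from 0.8 to 1.8. That makes 2 × 3 × 3 × 8 = 144 scenarios. The RNI count exceeds the truth in all of them. The ratio runs from 1.08 to 10.7, with median 1.67: 52 scenarios lie below 1.5, 37 between 1.75 and 2.5, and 23 above 2.5. The ratio is smallest where most women are truly inadequate and largest where few are.

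**The case against.** Four points can be made for the plan.

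- **No cut-off is written down.** The article says that means are compared with the RNI and that percentages are reported. It does not say that each woman below 100% of the RNI is inadequate, and the percentages could be percentages of the RNI. This stands in part: a reader might infer a fixed classification rule, and the text does not go that far. But the comparison is made in order to determine adequacy, so below-RNI intake would be read as inadequate unless the wording changes.
- **The error depends on what the RNI is.** The article does not define it and its source is not at hand. If the RNI were itself an average requirement, the overstatement in Step 1 would vanish. This stands, and it is why the point is conditional.
- **Energy is covered by the same sentence.** If the energy reference is an average requirement, the argument does not apply to it, and subtracting a margin would set the threshold too low. This stands; the point is limited to nutrients.
- **Little depends on it.** In Study aims, Objective 2 names "chrononutrition (energy and nutrient intake, energy and nutrient distribution, meal frequency, eating window, breakfast-skipping, late-night eating and intermittent fasting") as factors to be associated with circadian rhythm; adequacy is not listed. Adequacy is neither a main nor a secondary outcome under Outcomes measures, and Statistical analysis puts intake, not RNI status, into the models. The recommendations foreseen in the Discussion concern maternal circadian rhythm. A reader might infer that the association results or those recommendations are compromised; the article does not support that.

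**Conclusion.** The point holds in a conditional and limited form. Assuming that a nutrient's RNI is set above the average requirement, counting women whose 3-day mean falls below it as inadequate overstates the prevalence of inadequate intake. The direction was the same in every scenario tried.

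The size cannot be fixed from the article. It is about 1.7- to 3.1-fold when mean intake is at the RNI, requirement CV is 10–15% and usual-intake CV is 20–30%, and smaller or larger elsewhere. A reader might take away that the figure is roughly doubled. No figure in the article supports that, and only 37 of the 144 scenarios lie between 1.75 and 2.5.

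Energy is excluded if its reference is an average requirement. One descriptive result is affected; the objectives, association analyses and sample size are not. This is a minor improvement, not a threat to the study's conclusions.

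**What to change.** 1. Report nutrient intake as a percentage of the RNI, and describe women under it as below the RNI, not as inadequate.
2. For each nutrient with an average-requirement value, report the share of women below that value. Before counting, adjust the 3-day means for day-to-day variation, shrinking them towards the group mean. The three recorded days allow the within-woman variance to be estimated, so the daily values must be kept as well as the means, and the weekday–weekend difference should be allowed for.
3. For a nutrient without such a value, stop at item 1.
4. Handle energy separately, stating which reference is used and what it represents.
5. State in one sentence what the RNI in the cited source represents.

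The cost is wording and a short descriptive analysis; no new data are needed. Average-requirement values have to be listed nutrient by nutrient, and the reported inadequacy figure will be smaller.
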